#### Restricted predictor model

For each model XG, NN, EN and SVM, we will identify hyperparameters by a grid search with 10-fold stratified cross-validation, ensuring an approximately equal proportion of individuals with the outcome in each fold. We will use the AUC as the evaluation criterion for hyperparameter tuning.^30^

We will then compare the predictive performance of the different models when including the restricted set of predictors in the testing sample, using the DeLong method to assess statistical significance of the difference. We will also produce an ensemble prediction in the same way as described for the broad predictor model. If there is no model that performs better than the others in terms of AUC score (including the ensemble model) and calibration performance, we will consider the EN model as the final restricted predictor model.^15^ If there is a model with statistically significantly better AUC performance compared with the others (including the ensemble model), this model will be selected as the final restricted predictor model.

We favour the EN model in absence of clear superiority because this multivariate regression approach allows more transparency: the intercept and each predictor coefficient can be reported, allowing a prediction score for each study participant to be easily calculated by clinicians. This intercept of the model, which is a transformation of the baseline risk in the population, can also be changed to fit the particular population considered. In other words, an EN model would allow for greater transparency and scalability, including easy dissemination of the model as an online tool.^14^

Given the parameter selection inherent in an EN model, it is possible that even in the broad predictor model step it produces a model with fewer than 30 predictors. If this model already at the stage of the broad predictor model has a predictive performance superior to or equal to the other models, we will consider bypassing stage B of this protocol and using this model as the final model.

In the final model, we will assess the prediction performance in terms of the AUC in the subset of individuals who received a diagnosis of depression (ICD-10 code F32 or F33) in the previous 90 days. In the group of individuals aged 18–24 years, we will also consider testing the model performance separately for individuals initiating their SSRI in primary and specialist care settings.

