### Inclusion criteria

We will include all individuals aged 8–24 years who were born in Sweden and who initiated an SSRI after a wash-out period of 365 days free from any antidepressants during 1 January 2007 to 31 December 2020. The first initiation event per individual will be included.

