### Model development

Throughout the paper, we will employ different machine learning models: XGBoost (XG), neural net (NN), EN and support vector machines (SVM).^12 30^

We will develop all models in a sample (‘training sample’) using all data from 1 January 2007 to 31 December 2017. We will apply shrinkage procedures where appropriate, for example, by employing an EN.

We will validate all models in a sample (‘testing sample’) using all data from 1 January 2018 to 31 December 2020. That is, no random sampling will be performed for either training or testing sample.

As a secondary validation, we will validate the final restricted model in the period 1 January 2018 to 28 February 2020 to see if the model performance is influenced by the COVID-19 pandemic.

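### The final restricted model is chosen in the 2018–2020 testing sample and then evaluated in the same people; the effect is negligible if the elastic net is kept, but not if another model is declared superior

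*Protocol article*

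**What the plan says.** The Model development section defines two samples. Models are developed "using all data from 1 January 2007 to 31 December 2017". For the second sample the text reads "We will validate all models in a sample", the testing sample, "using all data from 1 January 2018 to 31 December 2020". It adds that "no random sampling will be performed for either training or testing sample".

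Under Model development, Restricted predictor model, the four learners are tuned by 10-fold cross-validation. Then: "We will then compare the predictive performance of the different models when including the restricted set of predictors in the testing sample", with DeLong tests of the differences and an ensemble as a fifth candidate. A model with a significantly better AUC than the others becomes the final model; otherwise EN does. The Abstract words the rule more loosely: any model showing AUC superiority is selected, otherwise EN.

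The section Model validation and goodness of fit gives DeLong 95% intervals for all AUCs. For the selected restricted model it adds Brier score, calibration, and sensitivity, specificity and predictive values at a 1% threshold. A secondary check reads: "we will validate the final restricted model in the period 1 January 2018 to 28 February 2020".

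There is also a shortcut. If the EN model from the broad stage "has a predictive performance superior to or equal to the other models, we will consider bypassing stage B" is possible; no sample is named for that decision.

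**The concern.** Choosing among five candidates is a development step. Here it uses the outcomes of the sample reserved for validation. A model that wins a comparison in a given sample tends to have done so partly by chance, so its AUC in that sample is biased upward. A DeLong interval treats the model as fixed in advance and does not reflect the choice.

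A non-EN winner would replace the model that the protocol prefers for its transparency. The figure supporting that replacement would be the one carrying the selection effect, and the plan holds no second sample in which to check it.

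**Working it through.** **Is any data left over?** The cohort is defined as "free from any antidepressants during 1 January 2007 to 31 December 2020", which is 14 calendar years. Training takes 2007–2017 (11 years) and testing 2018–2020 (3 years): 14 − 11 − 3 = 0. The secondary check (January 2018 to February 2020) lies wholly inside the testing period. External validation is named only as a possible next step.

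**Is there a stated figure to reproduce?** No. The article gives no sample size, event count or expected AUC, so the size below rests on assumptions.

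**Inputs.**
- From the article: five candidates; EN default; DeLong difference test; outcome prevalence about 1%.
- Assumed: 300–1,000 test events (30,000–100,000 initiators at 1%), true AUC 0.75 for every candidate, correlation ρ between AUC estimates of 0.80–0.95, two-sided 0.05.

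**Formulas.**
- Hanley–McNeil: SE² = [A(1−A) + (m−1)(Q1−A²) + (n−1)(Q2−A²)]/(mn), with Q1 = A/(2−A), Q2 = 2A²/(1+A), m events and n non-events.
- With A = 0.75, m = 300, n = 29,700: Q1 = 0.600, Q2 = 0.6429, A² = 0.5625. SE² = (0.1875 + 299×0.0375 + 29,699×0.08036)/8,910,000 ≈ 0.000269, so SE ≈ 0.0164.
- For 600 events SE ≈ 0.0116. For 1,000 events SE ≈ 0.0164×√(300/1,000) ≈ 0.0090.
- A difference is significant above 1.96×SE×√(2(1−ρ)). For 300 events and ρ = 0.80 this is 1.96×0.0164×√0.40 ≈ 0.020.

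Five correlated normal AUC estimates were simulated under two selection rules. The strict rule is the one in the Restricted predictor model section: a model must beat all the others significantly, else EN. The looser rule is one reading of the Abstract: the best model must beat EN significantly, else EN.

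| Events, ρ | Strict: non-EN chosen | Strict: mean bias | Strict, given a winner: excess; coverage | Looser: non-EN chosen | Looser: mean bias | Looser, given a switch: excess; coverage |
|---|---|---|---|---|---|---|
| 300, 0.90 | 0.30% | 0.00005 | 0.0155; 85% | 7.8% | 0.0013 | 0.0095; 92% |
| 300, 0.95 | 0.30% | <0.0001 | 0.0101; 90% | 7.8% | 0.0009 | 0.0067; 93% |
| 600, 0.90 | 0.30% | 0.00003 | 0.0103; 87% | 7.7% | 0.0009 | 0.0067; 92% |
| 600, 0.95 | 0.31% | 0.00001 | 0.0076; 91% | 7.8% | 0.0007 | 0.0048; 93% |

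The winner column includes wins by EN; with equal true AUCs, a non-EN winner behaves the same way.

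**Ranges over 300–1,000 events and ρ 0.80–0.95.**
- Strict rule: a non-EN model is chosen in about 0.3% of replicates, mean bias is about 0.0001 or less, and overall coverage is about 95%.
- Strict rule, given a winner: excess about 0.006 (1,000 events, ρ = 0.95) to 0.021 (300 events, ρ = 0.80), with coverage about 75–91%.
- Looser rule: a switch in about 8%, mean bias 0.0005–0.002.

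**Sensitivity.** Widening to 100–600 events, AUC 0.70–0.80 and ρ 0.70–0.95 gives, for a strict-rule winner, an excess of about 0.007–0.047 and coverage of about 64–91%.

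**If one candidate is truly better** by 0.005–0.01 (AUC of the others 0.75, 300–600 events, ρ 0.80–0.95), the strict rule switches to it in about 0.6–52% of replicates. The winner's AUC is then overstated by 0.002–0.019, with coverage 81–95%.

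**The case against.** The strongest reply is that the rule is conservative. EN is kept for transparency, not because it came first, so on the default path its AUC is essentially unbiased. A switch needs significance, which is rare when the models are equal. All candidates' AUCs are reported with intervals, so readers see more than the winner. This stands, and it limits the size of the point.

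A reader might infer four stronger things.

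- *That the reported AUC is generally inflated by 0.002–0.009.* That is the expected excess from always taking the best of five. The plan does not do this.
- *That the temporal validation fails.* Fitting and tuning use 2007–2017, and predictor importance is computed in the training data. Only a choice among five already fitted models uses 2018–2020, and the Generalisability section claims only some generalisability over time. The broad ensemble, with its fixed equal weights, is not affected by this choice.
- *That the stage-B bypass and the depression subset also reuse the testing sample.* The article names no sample for either, so this cannot be asserted.
- *That the remedy is free.* Out-of-fold AUCs are slightly optimistic after tuning and after choosing predictors in the full training data. A late slice takes events from training.

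What remains is that the text itself fixes the only hold-out as the place where the model is chosen. This is not a detail left to an unseen analysis plan.

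**Conclusion.** The point holds as a design weakness of limited size. The testing sample both selects and evaluates the final restricted model, nothing independent remains, and the intervals ignore the selection. If EN is kept, the consequence is negligible. If a non-EN model is declared superior, its AUC is overstated by about 0.006–0.021, with 75–91% coverage, if the models are truly equal, and by less if it is truly better.

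These sizes depend on event counts, AUC correlation and a significance level that the article does not give. The change is a cheap improvement, best made before the testing sample is opened. It is not a defect that invalidates the study.

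**What to change.** State that the model type, and any decision to bypass stage B, will be made within 2007–2017. Use either the out-of-fold predictions from the cross-validation already planned or a late time slice held out of training. Freeze the chosen model, then evaluate it once in 2018–2020 for AUC, calibration and threshold performance. Report the other models' test AUCs descriptively. Describe the January 2018 to February 2020 analysis as a sensitivity analysis within the testing sample.

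The cost is protocol wording plus one of two small losses: slight optimism in the out-of-fold AUCs used for the choice, or fewer training events if a slice is held out. In either case the AUC in 2018–2020 is free of model-choice bias and its DeLong interval keeps nominal coverage.

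If selection is to stay in the testing sample, label the chosen model's AUC as post-selection and correct it by bootstrapping the selection step.

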**Methods and analysis:**

Using Swedish national registers, we will identify individuals initiating an SSRI aged 8–24 years 2007–2020. We will develop: (A) a model based on a broad set of predictors, and (B) a model based on a restricted set of predictors. For the broad predictor model, we will consider an ensemble of four base models: XGBoost (XG), neural net (NN), elastic net logistic regression (EN) and support vector machine (SVM). The predictors with the greatest contribution to predictive performance in the base models will be determined. For the restricted predictor model, clinical input will be used to select predictors based on the top predictors in the broad model, and inputted in each of the XG, NN, EN and SVM models. If any show superiority in predictive performance as defined by the area under the receiver-operator curve, this model will be selected as the final model; otherwise, the EN model will be selected. The training and testing samples will consist of data from 2007 to 2017 and from 2018 to 2020, respectively. We will additionally assess the final model performance in individuals receiving a depression diagnosis within 90 days before SSRI initiation.

The aims are to (A) develop a model predicting suicidal behaviour risk after SSRI initiation among children and youths, using machine learning methods, and (B) develop a model with a restricted set of predictors, favouring transparency and scalability.

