### Model validation and goodness of fit

Overall classification performance using area under the receiver operating characteristic curves (AUC) will be estimated for all models; 95% CIs will be calculated using DeLong’s method.^12 27^

For the broad variable search model and for the selected restricted predictor model, we will assess the predictive performance of the trained models using: Concordance Index, Brier Score and a calibration plot.^12 14^

For the broad variable search model and for the selected restricted predictor model, we will also asses sensitivity, specificity, positive and negative predictive values at the risk threshold of 1%, given that this is the approximate prevalence of suicidal behaviour within 30 days after SSRI initiation in Swedish registers.^25^ That is, any child, adolescent or young adult with a predicted risk greater than 1% have a risk that is higher than what is expected in the population, and can therefore be considered ‘high-risk’.^14 28^ We will also report calibration performance at a 2% and 5% risk cut-off.

The impact of different risk score cut-offs could be further evaluated in future work—however, continuous risk scores could provide a more flexible idea of individual risk as compared with risk cut-offs.^28^

We will follow the Transparent Reporting of a multivariable prediction model for Individual Prognosis or Diagnosis (TRIPOD) guidelines.^29^

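### The rule for choosing the final restricted model contradicts itself on calibration and, read literally, returns elastic net when two other candidates tie with each other but both beat it

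*Protocol article*

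**What the plan says.** Under Model development, Restricted predictor model, the protocol article compares XGBoost (XG), neural net (NN), EN, support vector machine (SVM) and their ensemble in the testing sample, "using the DeLong method to assess statistical significance of the difference". Two sentences then set the choice.

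- Fallback: "If there is no model that performs better than the others in terms of AUC score (including the ensemble model) and calibration performance", then "we will consider the EN model as the final restricted predictor model".
- Selection: "If there is a model with statistically significantly better AUC performance compared with the others (including the ensemble model), this model will be selected".

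The abstract (Methods and analysis) states the rule as "If any show superiority in predictive performance as defined by the area under the receiver-operator curve, this model will be selected as the final model". In every remaining case EN is its default. It does not mention calibration and names no comparator.

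Under Model validation and goodness of fit, AUC is planned for every model. The Brier score and calibration plot are listed for the broad model and "for the selected restricted predictor model, we will assess the predictive performance of the trained models using" these measures, that is, for a restricted model already chosen.

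The reason given for the EN default is transparency: its coefficients can be published and used by clinicians when no rival is clearly better.

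**The concern.** This rule decides which model the study offers for clinical use. Three things are wrong with it.

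1. The fallback makes calibration part of the test; the selection sentence and the abstract do not. All models are tuned on AUC, which does not reward calibration, so the best discriminator need not be the best calibrated. The article's own introduction to the abstract asks for both properties.
2. The calibration results that the fallback needs are listed only for the model that comes out of the selection, not for the candidates going into it.
3. Superiority is required over every other candidate, not over EN. A tie at the top that excludes EN therefore produces the same answer as a tie that includes EN.

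Two analysts with the same results could name different final models, or EN could be kept after being shown significantly worse than several rivals, an outcome that the stated rationale does not cover.

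**Working it through.** The plan gives no test-set size, expected AUC, significance level or power for this comparison, so there is no figure of its own to reproduce. The first two steps are logic; the third is illustration.

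**Step 1: the rules side by side.** Let A = one model has significantly better AUC than all others, and B = that model is also better calibrated.

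| A | B | Fallback sentence | Selection sentence | Abstract |
|---|---|---|---|---|
| no | no | EN | does not apply | EN |
| no | yes | EN | does not apply | EN |
| yes | no | **EN** | **that model** | **that model** |
| yes | yes | does not apply | that model | that model |

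The third row is a direct contradiction. It needs no assumed numbers. (In the second row, B refers to the model with the highest AUC.)

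**Step 2: the tie.** There are five candidates, so a winner must beat four rivals. Suppose XG and the ensemble (or XG and NN) each significantly beat EN but do not differ from each other. Neither beats all four, A is false, and EN is returned. The abstract could be read as asking only for superiority over EN; on that reading XG or the ensemble qualifies, which differs from the main text.

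**Step 3: how often the tie might occur.** A simulation applied the literal rule with paired DeLong tests at z > 1.96 and 300 replicates per setting.

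- From the plan: about 1% outcome prevalence; an equal-weight ensemble.
- Assumed: test sets of 30,000 or 60,000; normal scores; within-class correlation 0.80, 0.90 or 0.95; EN and SVM with true AUC 0.74; the ensemble approximated by the mean score.

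Percentage of replicates in which EN was chosen while significantly worse than at least two candidates:

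| Test set | Correlation | Two leaders (0.77, 0.77) | One leader (0.77, next 0.76) |
|---|---|---|---|
| 30,000 | 0.80 | 95.3 | 90.0 |
| 30,000 | 0.90 | 94.0 | 67.7 |
| 30,000 | 0.95 | 97.3 | 42.7 |
| 60,000 | 0.80 | 98.7 | 97.3 |
| 60,000 | 0.90 | 94.3 | 40.7 |
| 60,000 | 0.95 | 94.7 | 14.3 |

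The two-leader column is high by construction. With two equal true AUCs at the top, each significantly beats the other about 2.5% of the time, so no winner emerges in about 1 − 2 × 0.025 = 95%.

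The single-leader column shows the dependence on inputs. The ensemble's mean AUC was 0.770 to 0.771 at correlation 0.80, level with the leader, but 0.757 to 0.758 at 0.95, clearly below it.

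A second set-up drew correlated AUC estimates directly: XG 0.02 above EN; NN and SVM equal to EN; correlation 0.90 between base models and 0.95 with the ensemble; standard errors 0.016, 0.012 and 0.009. EN was chosen in about 95% of runs when the ensemble equalled XG, but in 6% to 67% when the ensemble lay 0.008 to 0.010 below XG.

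**The case against.** The strongest reply is that a high bar for displacing EN is deliberate. The second aim favours a transparent, scalable model, and the fallback only says that EN will be considered. That explains keeping EN when it is not clearly inferior. It does not explain keeping EN when several candidates significantly beat it, and it does not reconcile the two sentences on calibration. Discretion exercised after the test-set results are known does not settle the choice either.

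It can also be said that the contradiction arises only when AUC and calibration disagree. That is correct and limits the point. Reading the fallback as keeping EN only if no model is better on either measure does not help: a model better on calibration but without a significant AUC lead would then fall under neither sentence.

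Three stronger readings are tempting and are not supported.

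- A reader might infer that EN will usually be kept although inferior. The documents give no test-set size, AUC gaps or correlations, and the rate swings widely with them. An equal-weight average can also be pulled below its best member by weaker ones, so a tie between leader and ensemble is not assured.
- A reader might infer that calibration cannot be available when the choice is made. The validation section does not say that calibration is assessed only for the models it lists, and the predicted probabilities exist for every candidate. The two sections are misaligned; the calculation is not impossible.
- A reader might infer that a minimum AUC margin is needed, because a trivial gain could displace EN. Nothing in the documents requires one, and a winner must beat four rivals, not EN alone. A margin could itself keep a significantly worse EN.

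**Conclusion.** Wrong as written; it should be fixed. The contradiction on calibration and the fallback to EN in a tie that excludes EN both follow from the text alone. The mismatch with the validation section is a smaller, related inconsistency.

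The size is the choice of the study's final model in two situations: the AUC leader is not better calibrated, or two or more non-EN candidates tie and beat EN. The frequency of the first was not estimated. For the second, the simulated 14% to 97% with a single true leader shows that the mechanism can matter; it is not an estimate for this study.

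The point does not reach the validity of the study, because AUC with 95% confidence intervals is planned for all models and an inferior EN would be visible in the report.

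**What to change.** Before test-set results are seen, replace the two sentences with one rule that takes EN as the reference:

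1. Test each other candidate against EN with the paired DeLong test, at a stated significance level and with stated handling of the several comparisons.
2. Say whether calibration is a condition for replacing EN and, if so, by which measure.
3. Compute that measure for all five candidates and list it so in Model validation and goodness of fit.
4. Give a tie-break among candidates that beat EN, for example the highest AUC or the simpler model.
5. Bring the abstract, the validation section and the Restricted predictor model section into line.

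If the sponsor does want EN kept even when several candidates significantly beat it, the plan should say so and why. A minimum AUC margin is optional and for the sponsor to decide. The cost is wording and a few extra calibration calculations on predictions that will already exist.
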